## Abstract

**Introduction:**

Molecular hydrogen had been considered inactive in vivo but is an antioxidant that selectively reduces highly toxic reactive oxygen species (ROS). Animal studies have reported that hydrogen gas inhalation helped alleviate cerebral and cardiac ischemia-reperfusion injuries. In humans, hydrogen inhalation therapy is presently approved as a treatment under Advanced Medical Care B in Japan (jRCTs031180352: limited to adult patients who suffered out-of-hospital cardiac arrest and are in a continuous coma) and its effectiveness is being examined in a clinical trial. The Japanese government has introduced the “Advanced Medical Care System” to promote the development of drugs and devices under governmental regulations. Advanced Medical Care B is a system designed for unapproved or off-label drugs or medical technologies used in a clinical trial setting. Hepatectomy is generally performed with repeated hepatic blood-flow occlusion and then reperfusion (ischemia and reperfusion). No report, however, has been made on ROS inhibition by hydrogen inhalation therapy or its effectiveness in post-hepatectomy patients. Hydrogen gas inhalation in the early stages after hepatectomy is anticipated to inhibit liver dysfunction by inhibiting ROS.

**Methods and analysis:**

This study is a randomized, controlled, double-blind superiority trial, which will be conducted as a “specified clinical trial” in accordance with the Clinical Trials Act in Japan. Trial registration was prospectively completed before the first participant was enrolled.

The subjects will be patients who will undergo hepatectomy and will be allocated randomly into group A with hydrogen gas inhalation or group B with air inhalation after hepatectomy. The study will examine if hydrogen gas inhalation improves QOL of post-hepatectomy patients. The primary endpoint is patient QOL (score of a 40-item quality of recovery questionnaire, QoR40) on postoperative day 3 and the secondary endpoints are QoR40s besides that on postoperative day 3, grade of postoperative complications (Clavien-Dindo score), level of pain (Numerical Rating Scale (NRS)), amount of dietary intake, liver function, inflammation level, 8-hydroxydeoxyguanosine (urinary 8-OHdG) level, and number of pedometer-assessed steps.

**Ethics and dissemination:**

The study protocol has been approved by the Niigata University Central Review Board of Clinical Research. The findings of this study will be widely disseminated through peer-reviewed publications and conference presentations.

**Trial registration:**

jRCTs 03220332. Registered on 21 January 2021

## Strengths and limitations of this study

・The present double-blind RCT is expected to show that early clinical implementation of hydrogen gas inhalation after hepatectomy will inhibit ROS, thereby inhibiting liver dysfunction.

・Hydrogen gas inhalation could also be shown to contribute to early recovery of post-hepatectomy patients.

## Introduction

Molecular hydrogen had been considered inactive in vivo but is an antioxidant that selectively reduces highly toxic reactive oxygen species (ROS). In 2007, a rat study reported that hydrogen gas inhalation alleviated cerebral ischemia-reperfusion injuries [1]. Focal ischemia was produced by mild occlusion of the middle cerebral artery for 90 min, followed by reperfusion for 30 min. The rats inhaled 1–4% hydrogen gas mixed with inhalation anesthetics during the entire 120-min process. After 1 day, the infarct volume markedly decreased due to hydrogen gas inhalation. After 1 week, neurological symptoms improved, as indicated by improved motor function, and oxidative stress was reduced, as indicated by reduced 8-OHdG level near the infarct site.

There have been many reports on the inhibitory effect of hydrogen gas inhalation on ischemia-reperfusion injury in organs other than the brain [2, 3]. In rats, hydrogen gas inhalation reduced the cardiac infarct volume after coronary-artery ischemia and reperfusion, and cardiac function was protected [4]. Similar effects have also been reported in pigs [5]. Presently, hydrogen gas inhalation is approved as a treatment in Japan under Advanced Medical Care B (jRCTs031180352: limited to adult patients who suffered out-of-hospital cardiac arrest and are in a continuous coma), and its effectiveness is being examined in a clinical trial.

Hepatectomy is generally performed with repeated hepatic blood-flow occlusion and then reperfusion (ischemia and reperfusion). No report, however, has been made on ROS inhibition by hydrogen inhalation therapy or its clinical effectiveness in post-hepatectomy patients. Hydrogen gas inhalation in the early stages after hepatectomy is anticipated to inhibit liver dysfunction by inhibiting ROS. The present double-blind RCT is expected to show that early (i.e., after liver ischemia-reperfusion) clinical implementation of hydrogen gas inhalation after hepatectomy will inhibit ROS, thereby inhibiting liver dysfunction. Furthermore, hydrogen gas inhalation may be shown to contribute to early recovery of post-hepatectomy patients.

## Methods/design

This study is a prospective randomized, controlled, double-blind superiority trial which will be conducted as a “specified clinical trial” in accordance with the Clinical Trials Act in Japan. The study will involve 68 patients with hepatobiliary disease and who will undergo hepatectomy at Kansai Medical University Hospital in Japan. The subjects will be allocated randomly into group A (hydrogen gas inhalation group: 34 subjects) and group B (air inhalation group: 34 subjects). Groups A and B will receive 1200 ml/m hydrogen gas and 1200 ml/m air, respectively, via nasal cannula. The respective gas will be administered at least 1 h per time and three times per day, totaling 8 h or less. Air will be used as the placebo comparator to detect the effectiveness of hydrogen inhalation therapy. The air will have no odor, color, or additional effect on postoperative recovery. Moreover, post-hepatectomy patients are typically on room air. Face-to-face adherence reminder sessions will take place at the initial inhalation and at each study visit thereafter. This session includes notification of the total time count of the inhalation period and reinforcement that the study gas may be hydrogen gas or air. No concomitant treatments are prohibited. If a subject will require oxygen, it will be administered via an oxygen mask placed over the nasal cannula. The trial participation period starts after consent attainment and ends at postoperative hospital discharge. The period is expected to be approximately 14–21 days based on our previous experience. The 40-item quality of recovery questionnaire (QoR40) will be used to assess postoperative QOL [6]. The questionnaire will be distributed preoperatively to patients who will independently fill it out themselves. The results will be totaled (perfect score: 200 points) to evaluate postoperative patient satisfaction and recovery level (reference material in the appendix at the end of this paper). The questionnaire survey will be conducted at 10 AM on postoperative day 3.

The results of previous reports infer that hydrogen gas inhalation has wide effects on many aspects, such as on inflammation and liver function, by inhibiting ROS [1–5, 7–10]. The primary endpoint, therefore, is established as the QoR40 on postoperative day 3.

### Sample size estimation

In the field of this study, the QoR40 is constructed from 40 items related to “physical comfort,” “emotional state,” “physical independence,” “psychological support,” and “pain.” The maximum score per item is 5 points and the perfect total score, therefore, is 200 points [6]. In hemodialysis patients, it has been reported that symptoms of fatigue were reduced by approximately 30% using a dialysate containing dissolved molecular hydrogen [11]. Molecular hydrogen might affect particularly “physical comfort” and “emotional state” among the 20 items of the QoR40. The results will be considered clinically meaningful if hydrogen gas inhalation is to improve the items of “physical comfort” and “emotion state” by approximately 20%. If such improvement in scores occurs, the hydrogen gas inhalation group will be estimated to score approximately 16 points more than the air inhalation group and to have an average of approximately 153 points. When factors are considered, the estimated average of the hydrogen inhalation group will be 151 points, that of the non-hydrogen inhalation group will be 137 points, and the variance of data 30 points (same in both groups). If α-error and power are set at 0.20 and 70%, respectively, for a two-sided test, then 31 subjects per group (total of 62 subjects) will need to be enrolled in this study. If it is estimated that approximately 10% of the subjects will drop out, the target number of subjects will be 68.

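### The sample-size paragraph labels its spread a variance of 30, but its own 31 per group follows only if 30 points is the standard deviation

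*Protocol article*

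**What the plan says.** All the planning inputs are in the protocol article, section Sample size estimation.

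- Means: "the estimated average of the hydrogen inhalation group will be 151 points" and "that of the non-hydrogen inhalation group will be 137 points", a difference of 14.
- Spread: "the variance of data 30 points (same in both groups").
- Error rates: "If α-error and power are set at 0.20 and 70%, respectively, for a two-sided test".
- Result: "31 subjects per group (total of 62 subjects").
- Drop-out: "If it is estimated that approximately 10% of the subjects will drop out, the target number of subjects will be 68".

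Methods/design splits the 68 equally, 34 to each group. The Statistical analysis section names an unpaired t-test with common variance for the primary comparison and sets the significance level at 5%, two-sided.

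**The concern.** A standard deviation and a variance that share the number 30 are very different assumptions. A variance of 30 is a standard deviation of 5.48 points, so a difference of 14 would be a standardised effect of 14/5.48 = 2.56. A standard deviation of 30 makes the same difference an effect of 14/30 = 0.47. Only one of these can lie behind 31 per group.

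At stake is whether the sample size can be checked from the text. Anyone who re-runs the calculation with the spread as labelled will conclude that 68 patients is far too many. With the spread that was actually used, the number only just reaches 70% power at an alpha of 0.20.

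The drop-out step in the same paragraph also deserves a check, because 68 less 10% is slightly below 62.

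**Working it through.** **Inputs.** Difference 151 − 137 = 14; two-sided alpha 0.20; power 70%; equal groups (all from Sample size estimation). Test: equal-variance two-sample t-test (from Statistical analysis).

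**Step 1: reproduce the stated 31 with a standard deviation of 30.**

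Normal approximation: n per group = 2 × SD² × (z₀.₉₀ + z₀.₇₀)² / difference²
= 2 × 900 × (1.2816 + 0.5244)² / 196 = 29.95, rounded up to 30.

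t-test: power comes from the noncentral t distribution with 2n − 2 degrees of freedom and noncentrality 14 / (30 × √(2/n)).

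| n per group | Noncentrality | Power, alpha 0.20 two-sided |
|---|---|---|
| 30 | 1.81 | 69.7% |
| 31 | 1.84 | 70.7% |

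The smallest n that reaches 70% is 31, which is the plan's figure.

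**Step 2: repeat with a variance of 30 (SD = √30 = 5.48).**

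Normal approximation: 2 × 30 × (1.2816 + 0.5244)² / 196 = 1.0, so 1 per group.

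t-test with 2 per group: noncentrality 14 / (5.48 × √(2/2)) = 2.56, 2 degrees of freedom, power 75.3%. So 2 per group is enough.

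**Step 3: could another reading rescue the variance label?** I tried alpha of 0.20, 0.10 and 0.05, one- and two-sided tests, power of 70% and 80%, and a difference of 16 (the gain mentioned earlier in the same paragraph). With a variance of 30, no variant needs more than 4 per group.

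**Step 4: drop-out.**

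- 68 × 0.9 = 61.2 evaluable, or 30.6 per group.
- 62 / 0.9 = 68.9, so 69 patients in total, or 70 with equal groups.
- A loss from 68 to 62 is 6/68 = 8.8%.

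**Step 5: power for the evaluable number** (SD 30, difference 14, t-test; 30.6 is treated as a continuous n).

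| n per group | Alpha 0.20 two-sided | Alpha 0.05 two-sided |
|---|---|---|
| 30 | 69.7% | 42.8% |
| 30.6 | 70.3% | 43.5% |
| 31 | 70.7% | 44.0% |

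**The case against.** The strongest reply is that this is one wrong word with no consequence. The spread is given in points, which is the unit of a standard deviation; a variance would be in squared points. With 31 per group printed in the next sentence, a statistician can recover the meaning. Nothing in the plan uses a variance of 30: the calculation used a standard deviation of 30, no interim analysis is planned, and the article provides for no check of the observed spread against the assumption. All of that stands, and it limits the point to a wrongly stated input. It does not make the statement right, and the error can be shown from the article's own figures.

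Two stronger readings are tempting but not supported.

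- **That the target of 68 is a material drop-out error, from multiplying by 1.1 instead of dividing by 0.9.** It is true that 61.2 is below 62. But the article says the loss is approximately 10%, and a loss of 8.8% leaves exactly 62. Power at 30.6 per group is still 70.3%. Nor can the method be inferred, because no formula is given: 31 × 1.1 = 34.1 and 31 / 0.9 = 34.4 both round to the nearest whole number as 34, the group size in Methods/design.
- **That the mislabelled spread makes the sample size wrong.** It does not, because 31 per group is correct for the standard deviation that was used.

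**Conclusion.** The point holds as an error in a stated input. Under the article's own difference, alpha, power and test, 31 per group requires a standard deviation of 30 points; a variance of 30 would require about 2 per group. On the standard deviation scale the label understates the spread by a factor of 30/5.48 = 5.5. The correction changes neither the sample size nor the conduct of the trial.

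The drop-out figure is a minor note. A full 10% loss leaves about 61 evaluable patients, 30 or 31 per group, and the planned power of about 70% is essentially kept at an alpha of 0.20. That 70% does not carry over to the test as planned: at the two-sided 5% level in Statistical analysis the same numbers give about 43–44%. The mismatch between the two alpha levels is a separate and larger matter, which correcting the label does not resolve. It matters here because a power quoted without its alpha would mislead.

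These figures assume normally distributed scores, a common standard deviation of 30, a true difference of 14, and losses spread evenly over the groups.

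**What to change.** In Sample size estimation, replace the variance wording with 'a standard deviation of 30 points in each group'. The 31 per group and the target of 68 stay as they are.

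Optionally, add one sentence saying that 68 enrolled patients leave about 61 evaluable (30 or 31 per group) after a full 10% loss, and give the power for that number with its alpha: about 70% at two-sided 0.20, and about 43–44% at two-sided 0.05. The drop-out point by itself calls for no extra patients; this says nothing about whether the size is adequate for a 5% test.

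The cost is one or two sentences of wording, with no change to the design, the analysis or the patients' treatment.

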### Statistical analysis

For the primary analysis, an unpaired *t*-test with common variance (PPS analysis) will be performed to compare the mean of the QoR40 on postoperative day 3 between groups. The subject population to be analyzed will consist of patients who will have consented to trial participation; who will have been administered, according to schedule, at least the minimum dose of their respective gas for at least 2 days; and whose QoR40 on postoperative day 3 will have been measured. The daily minimum dose will be converted to the duration of administration (3-h duration per day) and will be administered in at least 6 h to less than 7 h. In the sensitivity analysis, a *t*-test will be used on the per-protocol population and similarly on a population which includes patients who received insufficient gas. Content with a focus on the non-unique content will be noted in a statistical analysis plan. No compensation for missing data will be made. The statistical significance level will be set at 5% (two-sided) with a confidence interval of 95% (two-sided). No interim analysis will be performed.

For other items, the effects of hydrogen inhalation will be examined by parameters, such as the extent of hepatectomy (segmentectomy or more extensive resection vs subsegmentectomy or less extensive resection) and hepatic ischemia time (30 min or more vs less than 30 min). In addition, comprehensive and exploratory examinations will be performed, including a comparison of patients with high QoR40 scores and patient characteristics.

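### The trial is sized at a two-sided alpha of 0.20 but tested at 5% two-sided, so power for the planned 14-point difference is about 44%, not 70%

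*Protocol article*

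**What the plan says.** **Sample size estimation.** The planning means are 14 points apart: "the estimated average of the hydrogen inhalation group will be 151 points, that of the non-hydrogen inhalation group will be 137 points". The spread is given as "the variance of data 30 points (same in both groups". The error rates and the result follow in one sentence: "If α-error and power are set at 0.20 and 70%, respectively, for a two-sided test, then 31 subjects per group", 62 in total, raised to 68 for about 10% dropout. Methods/design splits the 68 equally: "group A (hydrogen gas inhalation group: 34 subjects) and group B (air inhalation group: 34 subjects".

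**Statistical analysis.** The primary analysis is an unpaired t-test "with common variance (PPS analysis) will be performed to compare the mean of the QoR40 on postoperative day 3 between groups". The same paragraph continues: "The statistical significance level will be set at 5% (two-sided) with a confidence interval of 95% (two-sided". It makes no exception for the primary endpoint and states that there is no interim analysis, so no alpha is spent elsewhere. The abstract and Methods/design both call the study a superiority trial.

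**The concern.** Two significance levels are fixed for one primary test. The sample size rests on a two-sided 20% level, while the decision rule and confidence interval rest on a two-sided 5% level. The 70% power belongs to the first and does not carry over to the second.

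Three things follow.

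- At the planned effect, the test as specified is more likely to miss the difference than to detect it.
- A non-significant result would be read against a stated power of 70% that does not apply to the test that produced it.
- With two levels in one protocol, a p-value between 0.05 and 0.20 could be argued either way once the result is known.

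A secondary defect is the label on the spread. A reader who takes 30 as a variance cannot reproduce the sample size.

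**Working it through.** **Inputs** (from Sample size estimation unless noted)

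- Difference: 151 − 137 = 14 points
- SD: 30 points (labelled a variance; checked in step 4)
- n = 31 per group, equal allocation (Methods/design)
- Planning: two-sided alpha 0.20, power 70%
- Analysis: two-sided alpha 0.05, unpaired t-test with common variance (Statistical analysis)

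**Step 1. Reproduce the plan's 31 per group.**

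Normal approximation: n = 2 × (SD/Δ)² × (z for 1 − α/2 + z for power)² = 2 × (30/14)² × (1.2816 + 0.5244)² = 29.95.

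The noncentral t calculation gives 30.28, rounded up to 31. This matches the plan. Power at 31 per group is 70.7%.

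Other settings at 70% power do not give 31 (t-test, rounded up):

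| Setting | n per group |
|---|---|
| 14 points, two-sided 0.05 | 58 |
| 14 points, two-sided 0.10 or one-sided 0.05 | 44 |
| 14 points, one-sided 0.20 | 18 |
| 16 points, two-sided 0.20 | 24 |

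Only one-sided 0.10, which has the same critical value as two-sided 0.20, also gives 31. So the calculation really used 0.20.

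**Step 2. Power of the test that will be run.**

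Standard error = 30 × √(2/31) = 7.62. Noncentrality = 14/7.62 = 1.837. Degrees of freedom = 60.

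- Alpha 0.20: critical t = 1.296, power 70.7%
- Alpha 0.05: critical t = 2.000, power **44.0%** (normal approximation 45.1%)

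Variations, all at two-sided 5%:

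| Case | Power |
|---|---|
| 68 × 0.9 = 61.2 evaluable (30.6 per group), 14 points | 43.5% |
| 31 per group, 14 points | 44.0% |
| All 34 per group analysed, 14 points | 47.5% |
| 31 per group, 16 points (the larger difference also mentioned in the section) | 54.2% |

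**Step 3. What 31 per group can show at 5%.**

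- Half-width of the 95% CI, if the observed SD is 30: 2.000 × 7.62 = 15.2 points. This is also the smallest observed difference that reaches significance.
- An observed difference of exactly 14 points: t = 1.837, p = 0.071, 95% CI −1.2 to 29.2.
- True difference for 70% power: about 19.2 points.
- For 14 points with 70% power: 57.7, so 58 per group, 116 evaluable; 116/0.9 = 128.9, so 129 enrolled.
- For 14 points with 80% power: 73.1, so 74 per group, 148 evaluable; 148/0.9 = 164.4, so 165 enrolled.

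**Step 4. Is 30 a variance or an SD?**

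If 30 were a variance, SD = √30 = 5.48. At two-sided alpha 0.20, 2 per group would give 75% power and 3 per group 93%. That is nowhere near 31, so 30 must be the SD.

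**The case against.** The arithmetic in the sample size section is right. It discloses alpha 0.20 in the same sentence as 70% power, and at that alpha the power is there. The article never claims 70% power at 5%. The relaxed level may have been a deliberate choice for an early study, with its rationale in the full protocol. This stands as far as it goes: the fault is a conflict between two sections, not a miscalculation. But the article assigns 5% to the primary test without exception and uses the word exploratory only for the secondary endpoints and other items. A rationale for 0.20 elsewhere would explain the choice without removing the conflict, and this is not a detail left to an analysis plan, because the protocol itself fixes both levels.

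Two qualifications are fair. The 15.2-point threshold and the non-significance of an observed 14 points hold only if the observed SD is near 30; with 31 per group, 14 points would be significant if the SD were below about 27.5 (14 / (2.000 × √(2/31))). And the mislabelled variance is minor: the unit of points already suggests an SD, and relabelling it changes neither the sample size nor the power.

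**Conclusion.** The concern holds. The protocol's two levels for the primary test contradict each other, and the stated 70% power does not apply to the 5% test it specifies. At 31 per group that power is 44.0% for the planned 14 points.

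This rests on reading 30 as the SD, on the planning difference of 14 points, and on 31 evaluable patients per group. Neither analysing all 34 per group (47.5%) nor using the 16-point difference (54.2%) brings it near 70%. The primary set is per-protocol and requires a minimum amount of gas inhalation, so exclusions beyond the assumed 10% would lower it further. This must be corrected because it concerns the decision rule and the stated power of the primary endpoint.

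**What to change.** Use one significance level in both sections and state the power that belongs to it.

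1. **Keep 5% and 68 patients.** Rewrite the end of the sample size paragraph along these lines: *With 31 evaluable patients per group, a standard deviation of 30 points and a two-sided 5% t-test, power is 44% for a difference of 14 points and 70% for a difference of about 19 points.* This costs a wording amendment and a less favourable stated power. It makes the document correct but leaves the trial with low power for 14 points.
2. **Keep 5% and restore the power.** This needs 116 evaluable patients (about 129 enrolled) for 70%, or 148 evaluable (about 165 enrolled) for 80%, against the 68 planned.
3. **If 20% was the intended level for the primary test,** say so in both sections, report an 80% CI beside the 95% CI, and do not present a result at that level as a demonstration of superiority. Take this route only if documents dated before the first enrolment (9 March 2021) show that intention. The trial is recruiting, and the Blinding section says the principal investigator and the person responsible for the statistical analysis know the allocation, so relaxing the level now would not be credible.

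In every case, replace the word variance by standard deviation for the figure of 30.
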